### Study design and setting

This is a multi-centre, blinded, randomized study (Fig. 2). The study will take place at five emergency medicine (EM) residency programs across North America (4 Canadian- and 1 US-based centres). All EM residents PGY1–5 are eligible and will be invited to participate. Written consent will be obtained from all study participants. There are no exclusion criteria. We received research ethics board approval from all participating institutions.

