### Instructional methods

Residents at each study site will be assigned to receive either DP + ML, or self-guided practice using a computer-generated randomization process. Participants will be blinded to the study group assignments. For practical purposes, we will cluster 4–6 participants with 1 instructor who will facilitate the training using one of the two instructional methods. This group size aligns with recommendations from surgical education literature for procedural skill training that demonstrates the optimal trainee:instructor ratio for procedural skills training [37]. All instructors are board certified emergency physicians with expertise in procedural skill training. Prior to the session, each instructor will receive an introduction to the task trainer, a briefing on how to conduct the training and a standardized approach to BAC performance. The instructors assigned to the DP + ML session will also receive an introduction to the BAC checklist and explicit instructions to facilitate mastery learning followed by deliberate practice [38]. The instructors assigned to the self-guided practice session will be told explicitly that they can only provide feedback following a participant request. They will be instructed by the study investigators on the necessary steps for BAC performance.

Both groups will receive an introductory lecture to surgical airway performance and a demo of the BAC on the task trainer by the session instructor. Participants will then complete a pre-training survey assessing self-confidence and prior cricothyroidotomy experience, followed by a video-recorded performance of a BAC using an upper body task trainer (head and neck from a Laerdal SimMan) to assess baseline performance before training begins.

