### Statistical analysis

The survey data will be analyzed using descriptive statistics. The primary outcome (GRS) score will be evaluated using a repeated measures ANOVA with between subject factor of instruction (DP + ML or SG group) with one within subject factor of assessment repeated 3 times (pre, post, and retention). SPSS software (SPSS Inc. 18.0, Chicago IL) will be used for data analysis. 2-sided *P* < 0.05 is considered statistically significant for the primary outcome. Interrater reliability (IRR) for the reviewers’ scores will be analyzed using an intraclass correlation, after reviewing the same 20 videos. If a target IRR of ≥0.7 is achieved, the rest of the videos will be scored by one reviewer. Confidence ratings will be compared with GRS at pre-training, post-training and retention using Spearman’s correlations.

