Currently, there is a paucity of data to inform preferred methods of simulation-based procedural training. McGaghie et al. concluded in their 2011 meta-analysis that “only a small number of studies were identified that address head-to-head comparative effectiveness of SBME with deliberate practice and traditional clinical education or a preintervention baseline” [2]. A more recent systematic review and meta-analysis concluded that “limited evidence suggests” the superiority of mastery learning SBME over other techniques [15]. The authors noted that few studies compare ML with other simulation-based instructional methods, such as self-guided practice, with mixed results. In one study, anesthesia residents learning ultrasound guided regional anesthesia were randomized to either DP + ML or self-guided practice. The authors reported that while performance improved among both groups, there were no differences in participant skill performance or retention between groups [8]. In contrast, a study of medical students learning ultrasound guided regional anesthesia techniques concluded that the deliberate practice resulted in fewer errors compared to self-guided practice [19]. Both of these studies are subject to important limitations including a small sample size at a single institution. There remains uncertainty as to whether these findings can be extrapolated among a larger study population across multiple sites. Recently, a large, comparative, single site study of undergraduate medical trainees concluded mastery learning with simulation is superior to simulation without mastery learning for peripheral venous catheter insertion [43]. This certainly supports the use of ML in the undergraduate setting, however, its utility in postgraduate training requires further study.

Our study addresses this by comparing two different simulation-based instructional methods for EM residents using a large sample size at multiple centres. This study design seeks to overcome the limitation of generalizability—common among other single site SBME-based studies. In addition, the rarity and relative novelty of the BAC procedure itself minimizes baseline variation in prior experience skill.

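### Prior cricothyroidotomy experience is collected but left out of the GRS model, which costs a little precision if the primary test is the post-training difference or the group main effect

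*Protocol article*

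**What the plan says.** All references are to the Protocol article.

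- **Instructional methods.** After the introductory lecture and the demonstration, participants in both groups "complete a pre-training survey assessing self-confidence and prior cricothyroidotomy experience". They then perform a recorded procedure "to assess baseline performance before training begins".
- **Statistical analysis.** On the survey: "The survey data will be analyzed using descriptive statistics". Confidence ratings are also correlated with GRS, but experience is not. The GRS is analysed by "repeated measures ANOVA with between subject factor of instruction (DP + ML or SG group) with one within subject factor of assessment", the assessments being pre-training, post-training and retention. No covariate is named, nor is the term of the ANOVA that carries the primary test.
- **Primary outcome.** The between-group GRS difference at post-training. GRS at 6–12 months is a secondary outcome.
- **Study design and setting.** Emergency medicine residents from PGY1 to PGY5 are eligible. "There are no exclusion criteria".
- **Discussion.** The rarity and novelty of the bougie-assisted technique is said to be a feature that "minimizes baseline variation in prior experience skill".

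**The concern.** The trial enrols across five training years without exclusions. The survey asks about cricothyroidotomy in general, whereas the article's argument for inexperienced learners rests largely on the bougie-assisted technique being new. Some residents may therefore arrive with relevant exposure, and the trial records which ones. The model described for the GRS does not use that record.

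If experience predicts GRS, two things follow for a comparison of post-training scores that does not adjust for it. The confidence interval is wider than it need be, and a chance difference between the arms in the share of experienced residents moves the estimate. A covariate named in advance deals with both and removes any temptation to adjust only after an imbalance has been seen.

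**Working it through.** **1. The plan's own figure.** Sample size determination states 80 per group, 80% power, a 1.3-point difference and α = 0.05 (two-sided in Statistical analysis). No SD is given, so the figure can only be solved backwards:

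- detectable difference in SD units = (1.960 + 0.842) × √(2/80) = 2.802 × 0.158 = 0.443
- implied SD = 1.3 / 0.443 = 2.93 points

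It is used here only as the 80% power reference.

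**2. How much variance experience could explain (assumed).** For a none/any covariate with prevalence p and a standardised difference d, R² = p(1 − p)d². The documents give neither p nor d. Assumed range:

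- p = 0.1, d = 0.3: 0.09 × 0.09 = 0.008
- p = 0.3, d = 0.8: 0.21 × 0.64 = 0.134

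**3. Gain for an unadjusted post-training comparison.** Power = Φ(2.802/√(1 − R²) − 1.960); equivalent extra sample = 1/(1 − R²) − 1.

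| R² | Power | Equivalent extra sample |
|---|---|---|
| 0 | 80.0% | 0% |
| 0.01 | 80.4% | 1.0% |
| 0.02 | 80.8% | 2.0% |
| 0.05 | 82.0% | 5.3% |
| 0.10 | 84.0% | 11.1% |

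The upper corner of the assumed range (0.134) gives 85.3% and 15.5%.

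**4. Chance imbalance.** With p = 0.2 and 80 per arm, the SD of the difference in prevalence is √(2 × 0.2 × 0.8/80) = 0.063. The chance of a difference of at least 10 percentage points is 2 × [1 − Φ(0.10/0.063)] = 11%. Such an imbalance would shift an unadjusted post-training estimate by 0.10 × 0.3 = 0.03 SD to 0.10 × 0.8 = 0.08 SD, against a detectable difference of 0.44 SD.

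**5. Dependence on the term tested.** Take an experience effect b per SD of experience at baseline and kb after training, with stable-skill variance 0.36 and assessment variance 0.36 (all assumed). The carry-through of imbalance into the estimate is:

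- post-training difference: kb
- change from pre-training (the pre-to-post part of group by time): (k − 1)b
- ANCOVA on pre-training GRS: b(k − β), where β = (kb² + 0.36)/(b² + 0.72)

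| b | k | Post only | Change | ANCOVA on pre-training GRS |
|---|---|---|---|---|
| 0.3 | 1 | 0.30 | 0 | 0.13 |
| 0.3 | 0.5 | 0.15 | −0.15 | 0 |
| 0.3 | 0 | 0 | −0.30 | −0.13 |
| 0.5 | 1 | 0.50 | 0 | 0.19 |
| 0.5 | 0.5 | 0.25 | −0.25 | 0 |
| 0.5 | 0 | 0 | −0.50 | −0.19 |

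A simulation with 80 per arm and 3,000 runs agrees to within 0.03. With a constant effect (k = 1), the change contrast gained nothing from the covariate: its simulated standard error was 0.135–0.136 without and 0.135–0.137 with it. The zeros for ANCOVA at k = 0.5 arise because β is exactly 0.5 under these variances; they are not a general property.

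**6. Gain when pre-training GRS is also a covariate.** For b = 0.3 and k = 1, experience explains 0.09/0.81 = 11% of post-training variance. Adding it to the unadjusted comparison cuts the residual variance from 0.81 to 0.72 (11%). Adding it to an ANCOVA on pre-training GRS cuts it from 0.56 to 0.54 (3.6%).

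**The case against.** The strongest reply is that the pre-training GRS already measures the skill that earlier exposure would produce, and that it enters the model as the first of three assessments. This stands in part. A reader might infer that differences in experience stay in the error term and imbalance goes uncorrected whatever is tested. The documents do not support that: a group-by-time test cancels an experience effect that is constant over time. The reply is incomplete, however. The primary outcome is a post-training difference, no ANOVA term is named as primary, and the change contrast over-corrects if training shrinks the effect of experience.

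A reader might also infer bias. Allocation is randomised, so chance imbalance is already reflected in the standard error, and the unadjusted comparison is valid.

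It is tempting to set aside the pre-training GRS because it follows the instructor's demonstration. That argument is weak: both groups receive a demonstration, and experience is self-reported after it too.

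Nor does the Discussion contradict the design: minimising variation in experience is not the same as eliminating it. The survey sentence does not say descriptive use is exclusive, since confidence ratings are also correlated with GRS.

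Finally, covariates are often left to an analysis plan, which is not shown here. That keeps the point minor. The article does, however, state the factors of the GRS model and a use for the survey data, so a collected baseline measure is left out of a stated analysis.

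**Conclusion.** The point holds as a minor and conditional one. Prior experience is collected and the stated GRS model does not use it. The loss arises for the post-training difference or for a group main effect. It does not arise for a group-by-time contrast when the experience effect is constant. It is a loss of precision, with no bias on average.

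The size rests on an assumed 1% to 10% of GRS variance explained by experience, for which the documents offer no figure. On that range power rises from 80% by about 0.4 to 4 percentage points, and by less once pre-training GRS is adjusted for. If almost no resident has prior experience, the gain is negligible.

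**What to change.** In Statistical analysis:

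1. Prespecify prior cricothyroidotomy experience (none versus any, the category fixed before scores are unmasked) as a covariate, alongside pre-training GRS, in the between-group GRS comparisons at post-training and at retention.
2. Name the adjusted post-training comparison as the primary analysis, so that it is clear which result decides the primary test.
3. Report the unadjusted difference as supportive.

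The cost is a sentence or two of text and one or two degrees of freedom. Both measures are already collected, so no further residents or assessments are needed.

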#### Deliberate practice and mastery learning

In the DP + ML group, the instructor will demonstrate the procedure following the list of essential steps, published previously [38]. These steps were selected using a modified Delphi methodology. Participants will perform each step under direct instructor observation in keeping with mastery learning techniques [8] and subsequent practice will follow principles of deliberate practice – with the goal of skill improvement using repetitive performance coupled with personalized feedback from the instructor. Chronometry will be introduced in later stages of practice through timed performance [20]. We chose to incorporate chronometry as an additional pedagogic intervention in later stages of learning to further incentivize practice with an objective feedback metric. The training session will be considered complete once the participant and instructor independently agree that competent skill performance is achieved.

#### Self-guided learning

In the self-guided learning group, participants will observe the procedure demonstrated by an instructor, followed by self-guided practice using the same equipment and working environment as the DP + ML group. During practice, feedback will only be provided following an explicit participant request. Participants will be informed that they can complete their training at their own discretion, once they report feeling comfortable with the procedure.

Finally, participants from both groups will perform a video-recorded attempt immediately following completion of their respective practice sessions and complete a post-training survey.

### Skill retention

Skill retention will be evaluated at 6 to 12 months following the initial training session. Due to logistical challenges related to resident schedules (e.g. away on elective, off-service), we require a 6 month time frame to maximize participation. Each participant will perform a video-recorded BAC on the same task trainer used during their training sessions followed by a post-training retention survey.

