**Methods:**

A multi-centre, randomized study will be conducted at four Canadian and one American residency programs with 160 residents assigned to either mastery learning and deliberate practice (ML + DP), or self-guided practice for BAC. Skill performance, using a global rating scale, will be assessed before, immediately after practice, and 6 months later. The two groups will be compared to assess whether the type of practice impacts performance and skill retention.

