### Retention

A key aspect of procedural skill acquisition is skill retention. Medical trainees are expected to demonstrate competence in performing a wide array of procedures, despite having limited exposure to practice opportunities [21]. Acute care physicians face the additional challenge of performing these procedures with little to no warning in stressful situations with unstable patients.

Several studies have looked at SBME to improve skill retention yielding variable results. Skill decay ranges from 2 weeks to 14 months for procedures such as ACLS, shoulder dystocia and cricothyroidotomy skills, with the most common retention interval being 6–12 months [22–25]. These differences are perhaps unsurprising, given that there are a number of different factors that influence retention including degree of overlearning, performance conditions during retention evaluation, task characteristics, and unmeasured individual differences [26–30]. While it appears that 6–12 months is a reasonable timeframe to expect for skill retention, there is uncertainty regarding the training approach best suited to optimize skill performance over time.

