### Primary outcome

The primary outcome is the difference in skill performance of BAC between the two groups at post-training, assessed using a previously validated 7-point global rating scale (GRS) [22, 39]. Video recordings will be scored by three independent airway experts (2 Royal College certified emergency physicians, 1 staff anesthesiologist) trained in BAC. All reviewers will receive training from study investigators followed by practice video review to ensure scoring standardization. All reviewers will be blinded to the subjects’ identities and group allocation.

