### Secondary outcomes

Secondary outcomes include participant feedback and chronometry after the initial training and retention sessions. Performance time begins when the participant first palpates the neck of the task trainer and ends with successful ventilation. Time scores will be measured using video review. Participant feedback will be collected with pre and post-training surveys. Skill performance (measured using GRS) at 6–12 months will also be compared.

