This study has several limitations. Given that both teaching and testing occur with a low-fidelity simulator, our study is designed only to assess procedural skills rather than the decision making and non-technical skills of an interprofessional resuscitation. Due to logistical constraints, retention data collection will take place between 6 to 12 months rather than at a single point in time. Although all study participants will voluntarily enrol, we cannot guarantee their motivation to learn and improve, which is a key aspect of deliberate practice.

In conclusion, this study will have important implications for residency training as it will provide insight for medical educators involved in the design of simulation-based technical skills training. High quality simulation-based skills training is a promising method to improve clinical outcomes and patient safety [44]. At a system-based level, this study will aid administrators and medical education leaders in their decision making for resource allocation towards skills training and inform future curricular designs.

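### Retention is tested anywhere from 6 to 12 months but analysed as a single time point, and the Abstract calls it 6 months: a small loss of precision, and a blind spot for timing differences between arms

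*Protocol article*

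**What the plan says.** Most of the article is consistent. The Background, the objectives, the Skill retention section, the Secondary outcomes section and the Discussion all place the retention test between 6 and 12 months after training. The operative sentence is "Skill retention will be evaluated at 6 to 12 months following the initial training session". The reason given is residents' availability: "we require a 6 month time frame to maximize participation". That figure is the width of the window, not the time of the test. The Discussion lists the spread as a limitation: "retention data collection will take place between 6 to 12 months rather than at a single point in time".

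Two places do not fit. The Methods paragraph of the Abstract says that performance "will be assessed before, immediately after practice, and 6 months later". The Statistical analysis section specifies a repeated measures ANOVA with instruction as the between-subject factor and "one within subject factor of assessment repeated 3 times (pre, post, and retention". A resident tested at month 6 and one tested at month 12 therefore share one level, and no elapsed-time term is stated.

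On status, "The primary outcome is the difference in skill performance of BAC between the two groups at post-training", while retention appears under Secondary outcomes: "Skill performance (measured using GRS) at 6–12 months will also be compared".

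**The concern.** The time since training can differ twofold between residents. The Background treats retention as depending on time, and says it is uncertain which training approach best preserves performance. If skill falls between months 6 and 12, three things follow under the stated model:

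- Variation in interval goes into the error term, although the interval can be calculated from the session dates.
- If one arm happens to be tested later, the difference in timing is read as a difference in retention, and nothing in the stated analysis would show it.
- If the two methods decay at different rates, the arm difference itself depends on the month of testing, and a pooled retention level averages over that.

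Separately, a reader of the Abstract would take the result as 6-month retention, which the Methods do not deliver.

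**Working it through.** **The plan's own figure.** There is no sample size calculation for retention. The only one gives 80 per group, 80% power and a GRS difference of 1.3, without a standard deviation (SD). Solving for it: SD = 1.3 / [(1.960 + 0.842) × √(2/80)] = 1.3 / 0.443 = 2.93. That is close to 3.0, the maximum if the 7-point scale runs from 1 to 7. This is a separate matter, and 2.93 is not used below. A larger SD would only make the effect of timing smaller.

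**Inputs from the article.** Window 6 to 12 months; 80 per arm; two-sided α = 0.05.

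**Assumptions (none is in the article).** Test times are spread evenly over the window; decay is linear at *b* points per month and equal in both arms; residual SD is 1.0 or 1.5 points; all 80 per arm return.

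**Step 1: added noise.** Even spread over 6 months gives variance 6²/12 = 3 months², or SD 1.73 months. Extra GRS variance is 3*b*², so SD′ = √(SD² + 3*b*²). For a contrast with 80% power at a fixed test time, power becomes Φ[2.802 × SD/SD′ − 1.960].

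| Loss, month 6 to 12 | *b* | 3*b*² | Power, SD 1.0 | Power, SD 1.5 |
|---|---|---|---|---|
| 0.25 | 0.042 | 0.005 | 79.8% | 79.9% |
| 0.5 | 0.083 | 0.021 | 79.2% | 79.6% |
| 1.0 | 0.167 | 0.083 | 76.8% | 78.6% |
| 1.5 | 0.250 | 0.188 | 72.9% | 76.8% |

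Example for a 1.0-point loss and SD 1.0: SD′ = √1.083 = 1.041, and 2.802/1.041 − 1.960 = 0.73, which gives 76.8%. The drop across the table is about 0 to 7 percentage points. In an extreme case, with half tested at month 6 and half at month 12 (variance 9 months²), a 1.0-point loss gives 70.7% at SD 1.0 and 75.7% at SD 1.5.

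**Step 2: chance imbalance.** If residents are scheduled individually and timing is unrelated to arm, the arm difference in mean interval has standard error 1.73 × √(2/80) = 0.27 months, so 95% of the time it lies within ±1.96 × 0.27 = ±0.54 months. At 0.1 to 0.2 points per month that is ±0.05 to ±0.11 GRS points. This is the noise of Step 1 seen from another side, not an addition to it.

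**Step 3: systematic imbalance.** At a 1.0-point loss over the window (0.167 per month), one arm tested on average 1 or 2 months later than the other would shift the contrast by 0.17 or 0.33 points. The stated model has no term that would reveal or remove this.

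**The case against.** The strongest defence is that the window is justified by resident schedules, disclosed as a limitation and shared by both arms. The Background calls 6 to 12 months a reasonable timeframe. Accepting some spread in return for better follow-up is a sound trade, and covariates are often left to an analysis plan that is not shown here. Most of this stands, and there is no case for changing the window. But disclosure does not alter the analysis. The article names its model, with retention as one level, so this is a stated specification and not merely an omitted detail. The Abstract's 6 months is a plain inconsistency within the document.

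Several stronger readings are tempting and are not supported:

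- **The Background proves decay within the window.** The sentence "Skill decay ranges from 2 weeks to 14 months" summarises findings across different procedures. It gives no GRS loss between months 6 and 12.
- **Timing alone could rival the 1.3-point target.** At 0.1 to 0.2 points per month, residents tested at months 6 and 12 differ by 0.6 to 1.2 points. That is a gap between two individuals, not between arm means, and both arms use the same window.
- **Chance imbalance is large because training runs in groups.** With groups of 5 there are 160/5 = 32 groups, 16 per arm. If each were retested as a block, the standard error would be 1.73 × √(2/16) = 0.61 months, or ±0.12 to ±0.24 points. The article does not say that retention is tested by group. It describes each participant's own test and cites individual schedules.
- **Imbalance is to be expected.** Residents are randomised within sites, so rotations and electives affect both arms. The documents give no mechanism for a systematic difference. They also give no safeguard against one, since retest dates are set after randomisation.
- **The primary result is compromised.** The retention level sits in the same ANOVA, but the post-training scores are recorded immediately after practice and do not depend on the retention interval.

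**Conclusion.** The point holds as a modest weakness in a secondary analysis plus one textual contradiction. The stated model ignores a known, variable interval, and the Abstract misdescribes the timing. With evenly spread timing and the assumed losses, the cost is at most about 7 points of power, and under 1 point if the loss is 0.5 or less. Chance imbalance is small. Notable bias needs a systematic arm difference in test dates, which is possible but not indicated. The decay rate, residual SD, timing distribution and full follow-up are all assumptions. With no decay in the window, only the wording of the Abstract and the labelling of the result remain at issue.

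**What to change.** Keep the 6 to 12 month window, and make these changes:

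1. In the retention comparison, include actual months from training to retest as a covariate. Alternatively, because timing is set after randomisation, give the adjusted result as a prespecified sensitivity analysis beside the unadjusted one. A separate linear model for the retention score is the simplest place for it, since the interval has no meaning for the pre and post assessments.
2. Add an exploratory arm × months term, to show whether decay appears to differ by method.
3. Report the distribution of the interval by arm.
4. Change the Abstract to 6 to 12 months.

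Testing both arms over the same period within a site is desirable where schedules allow. It should not be required, because it cuts into the flexibility the article says it needs.

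The cost is one degree of freedom for the covariate and slightly more analysis work. The dates are already needed to confirm that each test falls inside the window.
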